The project’s global hypothesis is that an intervention in the first 1000 days of life on the early programming factors related to childhood obesity will achieve more adequate early programming and will decrease the prevalence of childhood obesity. The risk of developing obesity in childhood will be lower when the number of factors accumulated in the individual in this critical first phase is decreased. This improvement in early metabolic programming will be reflected in a lower percent of body fat mass at 2 years of age, compared to the control group.

The aim of the project is to evaluate the effectiveness of a combined multifactorial educational and care intervention for preventing obesity and overweight in childhood, based on the concept of early programming, and developed during pregnancy and the first 2 years of life (the first 1000 days) by a multidisciplinary group in primary care. The specific objectives are:

To analyse the body fat mass at 2 years of age in a control group of children who reach this age between November 2017 and June 2019, belonging to two pediatric quotas of the Basic Health Zone (BHZ) of Puerto Real.

To analyse the body fat mass at 2 years of age in the intervention group of children, whose pregnancies begin between January and December 2018, belonging to four pediatric quotas of the BHZ of Puerto Real. 

To compare the body fat mass at 2 years of age between the control and intervention groups.

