The first visit within the pregnancy, birth and puerperium scheme is carried out between the 4th and 7th week of pregnancy. It is a 30-min visit in which the pregnant woman will receive an informative leaflet with general recommendations about a healthy pregnancy, where she will be introduced to the concept of early programming and its close relation to childhood obesity. Those pregnant women considered obese, who admit smoking, or who are believed to be unhealthy dieters, will be encouraged to take on the first workshop. 

Subsequent visits will monitor the risk factors, including whether new factors arise or persist, in which case workshop number one will be offered again or as a first time informative session. Early programming and childhood obesity will be the main and consistent ideas to be reinforced on each visit. The basic recommendations and lifestyle habits proposed to each pregnant woman will be related to these core concepts. 

Both workshops two and three will be offered to all pregnant women in the program. Those in the 14th–16th week of pregnancy will be encouraged to attend workshop number two, and those in the 30th-32nd week will be offered workshop number three.

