Recommendations during the first year:Promotion of breastfeeding (exclusively up to 6 months).Participation in local breastfeeding support groups.Avoidance of active/passive maternal smoking.Information on the advantages of breastfeeding for the prevention of childhood obesity.Recommendations for artificial lactation:Formulas with lower protein content are recommended up to 12 months, with a strong recommendation for children of overweight or obese mothers, gestational diabetes, and macrosomic newborns, if breastfeeding is not possible.Introduce complementary feeding between 4 and 6 months of life.Bottle feed should be slow, at least 15-20 min.Supplementary feeding tips:Reduce the protein content of animal origin between 6-12 months: 15 g/day of meat at 6 months and increase up to 40 g/day at the end of the first year.Tips to facilitate the introduction of fruits and vegetables to favor a more varied diet in the preschool stageAvoid the introduction of sweet flavors: honey, infusions, juices, etc.Tips for developing self-regulation of appetite/satiety.Identify signs of appetite/satiety in the infant.Do not force eating.Do not calm crying or night awakenings systematically with food.Vitamin D supplement (400 IU/day) during the first year.Tips for developing a secure attachment.Tips to develop adequate sleep habits.Recommendation of active play after 6 months.Avoid using screens, especially for sleeping and during meals.

Recommendations during the second year:Recommend growth formulas because of their lower protein content, compared to cows’ milk.Limit milk intake to about 500 mL per day.Restrict the intake of sweet flavors.Restrict the bottle as soon as possible.Maintain the recommendations in items 7–9 of the first year.

Most of the recommendations proposed in the intervention are not novel themselves, except for the recommendation to feed formulas with lower protein content to infants who are not breastfeeding. 

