#### 2.8.2. Dependent Variables

BMI at 2 years of life.Percentage of fat mass at 2 years of life.

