### 2.10. Data Analysis

For the statistical analysis of these data, the statistical program SPSS Version 22 software (IBM Corp, Armonk, NY, USA, 2015) will be used:

Descriptive analysis. The means and standard deviations for the quantitative variables and the absolute and relative frequencies for the qualitative ones will be determined.

Bivariate analysis. The Kolgomorov–Smirnov test will be used to determine if the quantitative variables are parametric; when the sample is less than 50, the Shapiro–Wilk test will be used. For the comparison of the dependent variables with qualitative independent ones, we will use the Student’s *t*-test and ANOVA for independent means as a test of statistical significance, and the Mann–Whitney U and the Kruskall–Wallis tests for the nonparametric ones. For independent quantitative variables, the Pearson and Spearman coefficients will be used.

Multivariate analysis. The analysis of the degree dependent variables with the independent variables will be carried out using the generalized linear model. For the linear regression, we will use the Gaussian family and as a function of the identity bond and for the binary logistic regression, the binomial family and the logit link function.

To detect differences, a significance level *p* < 0.05 will be used and the 95% confidence intervals will be calculated.

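### Section 2.10 tests each early-life factor against BMI and fat mass without accounting for study group, so a factor that merely differs between the groups can appear associated with the outcome

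*Protocol article*

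**What the plan says.** Section 2.8.2 names two dependent variables: "BMI at 2 years of life.Percentage of fat mass at 2 years of life". Section 2.8.1 lists 14 independent variables, maternal and infant. Study group is not among them.

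Section 2.10 chooses the bivariate test by type of variable. "For the comparison of the dependent variables with qualitative independent ones", it prescribes the t-test or ANOVA, or their rank counterparts. For continuous factors, "For independent quantitative variables, the Pearson and Spearman coefficients will be used". These procedures each take one factor at a time. The section does not say whether they run on all children or within each group, and it mentions no stratification.

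The multivariable step follows: "The analysis of the degree dependent variables with the independent variables will be carried out using the generalized linear model". Group is not named as a term there either.

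**The concern.** Several listed factors are direct targets of the programme. Section 2.7 gives advice on exclusive breastfeeding, vitamin D, the timing of complementary food and milk in the second year, and all four reappear in section 2.8.1. The Introduction expects the same programme to lower fat mass at 2 years. Under the trial's own hypothesis, then, group moves both factor and outcome.

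Two other routes lead the same way:

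- **Calendar time.** Section 2.1 calls the controls historical. By the Introduction's objectives they reach age 2 by June 2019. A pregnancy beginning in January 2018 leads to a second birthday in about October 2020 (9 + 24 months).
- **Measurement.** Under section 2.9, control data come from the one-year and two-year visits, while the intervention group is also asked at the newborn and six-month visits, so recorded durations may differ through recall alone. Skinfolds have one observer per quota, and the Introduction gives two quotas for the control group and four for the intervention group.

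If children from both groups enter one correlation or t-test, group is a common cause of factor and outcome. A factor with no relation to fat inside either group can then reach significance. What is at stake is the reading of which factors matter for fat or BMI at 2 years.

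**Working it through.** **The plan's figures.** The plan gives no figure for these associations. Its only related figures are the precision errors of about 9% and 7% in section 2.5, which confirm the group sizes and the loss rate used below. With a proportion of 0.5 (assumed), a population of 320 and 15% loss, the formula is 1.96 × √(0.25/m) × √((320 − m)/319):

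- 100 children, m = 85: 9.12%
- 150 children, m = 127.5: 6.74%

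Both agree with the plan after rounding.

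**Inputs.** From section 2.5: 100 control and 150 intervention children, so the intervention share is p = 150/250 = 0.6. From section 2.10: significance at p < 0.05, taken as two-sided (assumption). Also assumed are the between-group shifts dx (factor) and dy (outcome), in within-group SD; the document gives no SD or effect size, so a range is shown. The sign of a shift does not affect the error rate.

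**Induced correlation.** Let factor and outcome be independent within each group, and let q = p(1 − p) = 0.6 × 0.4 = 0.24. Pooling then gives

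r = q·dx·dy / √[(1 + q·dx²)(1 + q·dy²)].

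For dx = dy = 0.5: 0.24 × 0.25 / (1 + 0.24 × 0.25) = 0.06/1.06 = 0.057.

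For dx = 0.8, dy = 0.5: 0.096 / √(1.1536 × 1.06) = 0.087.

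If dy = 0 the numerator is zero, so r = 0 whatever the factor shift. The critical |r| is 0.124 at 250 children and 0.135 at 212 (85 + 127, after 15% loss).

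**False-positive rates.** Simulation with 20,000 replicates per setting, normal data, and no association within group:

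| Factor shift (SD) | Outcome shift (SD) | Induced r | Pooled, 100 v 150 | Pooled, 85 v 127 |
|---|---|---|---|---|
| 0.5 | 0 | 0 | 5.1% | 5.0% |
| 1.0 | 0 | 0 | 5.4% | 4.6% |
| 0.3 | 0.3 | 0.021 | 6.2% | 6.0% |
| 0.5 | 0.3 | 0.035 | 8.6% | 8.0% |
| 0.5 | 0.5 | 0.057 | 14.6% | 13.0% |
| 0.8 | 0.5 | 0.087 | 27.7% | 24.2% |
| 1.0 | 0.5 | 0.105 | 38.6% | 33.4% |
| 1.0 | 0.8 | 0.161 | 74.2% | 65.8% |

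The same correlation adjusted for group rejects in 4.7% to 5.1% of replicates in every row, with a mean r of about zero.

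**The case against.** The strongest reply is that the text never says the groups are pooled. The Introduction sets separate objectives for the control group, the intervention group and their comparison, and a fuller analysis plan might settle the point. This stands in part: pooling is an inference. But those objectives concern the level of body fat in each group, not factor associations. The named tests have no place for group as a second term, and separate runs by group, the one protection available to them, are not mentioned. Whole-sample analysis remains the natural reading.

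A second reply is that a bivariate step is unadjusted by design and a multivariable model follows. That is true, but group is not named as a term in that model, so as written it does not clearly supply the protection.

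A third is that large shifts are unlikely, because section 2.7 itself says most of the advice is not new. This also stands, and it points to the smaller rates in the table. Nor can the programme readily move every factor: newborn sex and maternal BMI at the first visit are examples.

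A reader might also infer three stronger points that the document does not support:

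- *That these tests are the trial's evidence for factor accumulation.* The Introduction hypothesises that "The risk of developing obesity in childhood will be lower when the number of factors accumulated in the individual" is decreased, but all three specific objectives concern body fat by group or between groups. Single-factor tests could not examine a count of factors in any case.
- *That every factor the programme shifts will correlate with fat.* The outcome must also differ between groups by some other route, and at moderate shifts most tests would still be non-significant.
- *That targeting distorts the slopes by a known amount.* Some mothers, including those "who admit smoking, or who are believed to be unhealthy dieters, will be encouraged to take on the first workshop", get extra attention, and lower-protein formula comes "with a strong recommendation for children of overweight or obese mothers, gestational diabetes, and macrosomic newborns". Slopes could therefore differ by group, but the document gives no basis for saying by how much.

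**Conclusion.** The point holds in a limited form. As section 2.10 is naturally read, its one-factor tests leave factor-outcome associations open to confounding by study group and period. Under assumed shifts at 100 v 150, the false-positive rate is about 6% to 15% for shifts of 0.3 to 0.5 SD in both variables. It is about 28% for a 0.8 SD factor shift with a 0.5 SD outcome shift, and about 5% when the outcome does not differ between groups. Larger shifts make it serious, but nothing in the document shows that they will occur. The result rests on pooling, which is inferred, and on shifts, which are assumed.

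The between-group comparison of body fat, which is the trial's main question, is not affected by this mechanism. Only the interpretation of individual factors is. The change is worth making before analysis because it affects which factors appear significant and costs almost nothing.

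**What to change.** Add to the bivariate paragraph of section 2.10 that each factor-outcome association is estimated adjusted for study group: a partial correlation (Pearson or Spearman) for continuous factors, and a two-way ANOVA or linear model with group as a term for categorical ones. State that unadjusted pooled coefficients will not be interpreted as evidence for a factor.

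Separate estimates for each group may be shown descriptively, which also lets a reader see whether the slopes differ. They should not be the default: control-only intervals would be about √(250/100) = 1.6 times as wide as those from all 250 children. The group-adjusted estimate keeps all the children and gives up one degree of freedom.

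The change is to wording and analysis code only, with no new data. It removes confounding by group and period, but associations within a group remain observational.

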### 2.8. Measures and Outcomes

#### 2.8.1. Independent Variables 

Weight gain during pregnancy. The difference in maternal weight between the first visit (weeks 4–7) and the last one (week 38) is calculated. If the weight on the last visit is not registered, it is calculated with the final pregnancy weight recorded in the hospital discharge report. It will be classified as adequate or excessive according to the accepted values of weight increase by the pre-gestational body mass index (BMI) of the Institute of Medicine (IOM) and National Research Council [61].Mother’s body mass index (BMI) at the first visit (weeks 4−7). This will be evaluated as a continuous measure.Maternal nutritional status. Classified as obesity, overweight, normal weight or low weight.Maternal smoking during pregnancy. Active smoker, passive smoker and non-smoker. The mother is considered an active smoker if she consumes any amount of tobacco.Gestational diabetes.Caesarean section.Newborn sex.Newborn weight. Registered in hospital visit (newborn measures).Duration of exclusive breastfeeding. Full months of exclusive breastfeeding are considered.Weight gain in the first four months. The difference in the infant’s weight between birth weight and fourth-month-postnatal weight at the visit is calculated as grams/day. As secondary outcomes, weight gain in the first six months and in the first year are also calculated.Introduction of complementary food, before or after 4 months of age.Vitamin D supplementation (400 IU/day) in the first year. Full months of supplementation are considered.Type of milk in second year. Classified according to the type of milk that was consumed the largest number of months: breastfeeding, growing milk or cow milk.BMI at 1 year of life.

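### The section 2.10 multivariable model names no study-group term and draws on a predictor list made up largely of what the intervention is meant to change, so it does not give the adjusted total effect that objective 3 needs

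*Protocol article*

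**What the plan says.** **The model.** Protocol article, section 2.10: "The analysis of the degree dependent variables with the independent variables will be carried out using the generalized linear model". It continues: "For the linear regression, we will use the Gaussian family and as a function of the identity bond", with a binomial family and logit link for logistic regression. It states no subset of variables, no selection rule and no group term.

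**The outcomes.** Section 2.8.2 gives BMI at 2 years and "Percentage of fat mass at 2 years of life".

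**The predictors.** Section 2.8.1 lists 14 independent variables. Among them are "Duration of exclusive breastfeeding. Full months of exclusive breastfeeding are considered" and "BMI at 1 year of life". Control versus intervention is not listed. A group code is mentioned only under masking (section 2.3).

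**The aim.** The third specific objective (section 1) is to compare fat mass at 2 years between the two groups. The hypothesis in the same section says how the benefit is expected to arise: "The risk of developing obesity in childhood will be lower when the number of factors accumulated in the individual in this critical first phase is" reduced.

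**The concern.** By the protocol's own hypothesis, many of the listed predictors are the steps through which the intervention works. Breastfeeding shows this: section 2.7 makes it a target ("Promotion of breastfeeding (exclusively up to 6 months"), and section 2.8.1 makes "Duration of exclusive breastfeeding" a predictor. BMI at 1 year is measured midway through the postnatal intervention and is an earlier value of one of the two outcomes. Section 2.8.1 even calls weight gain to six months and to one year secondary outcomes, inside the list of independent variables.

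A model built from this list answers which factors go with fat mass, not whether the intervention lowered it. If group is put in beside the list, a working intervention could be reported as having no independent effect. If group is left out, a study with a historical control has no adjusted comparison for its main question.

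**Working it through.** **1. Evaluable numbers.** Section 2.5 gives 100 controls, 150 intervention children, 15% loss and 320 births. After loss: 100 × 0.85 = 85 and 150 × 0.85 = 127.5. The only size-related figure in the protocol is a precision of about 9% and 7%. With half-width 1.96 × √(0.25/n) × √((320 − n)/319), n = 85 gives 9.12% and n = 127.5 gives 6.74%, so the figures reproduce at these numbers. (The 9% belongs to the controls and the 7% to the intervention group, the reverse of the printed order; that is a separate matter.) No effect size, SD, correlation or numerical power is given.

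**2. Sorting the 14 variables of section 2.8.1.**
- Fixed before the intervention can act, or unaffected by it (3): maternal BMI at weeks 4–7; maternal nutritional status, if it is classified from that BMI; newborn sex.
- Arising later (11): pregnancy weight gain, smoking in pregnancy, gestational diabetes, caesarean section, birth weight, exclusive breastfeeding, weight gain to 4 months, timing of complementary food, vitamin D, second-year milk, BMI at 1 year. Section 2.7 directly advises on five of these (smoking, breastfeeding, complementary feeding, vitamin D, milk type). The rest are possible consequences, with caesarean section the least clear.

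**3. Two readings of the model.**
- Group not included: no coefficient corresponds to objective 3.
- Group included beside the list: its coefficient is the total effect × (1 − mediated share).

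**4. Size under the second reading, BMI at 1 year only, outcome BMI at 2 years.** Assumptions, none from the documents: total effect d₂ = 0.40 SD, effect at 1 year d₁ equal to d₂ or half of it, 1-to-2-year correlation r. Remaining effect = d₂ − r·d₁; residual SD = √(1 − r²). Power = Φ(effect / (SD × √(1/85 + 1/127.5)) − 1.96). Unadjusted: 0.40/0.140 = 2.86, power 81.5%.

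| r | d₁ = d₂: effect left | power | d₁ = d₂/2: effect left | power |
|---|---|---|---|---|
| 0.3 | 70% | 55% | 85% | 72% |
| 0.5 | 50% | 38% | 75% | 70% |
| 0.7 | 30% | 22% | 65% | 74% |
| 0.8 | 20% | 16% | 60% | 82% |

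For % fat mass the same formula applies, with the correlation between BMI at 1 year and fat mass at 2 years, which is also not given.

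**5. Size under the second reading, a set of mediators.** Simulation with 85 against 127 children, six mediators explaining 30% or 50% of outcome variance, total effect 0.40 SD, 3,000 runs per case. Power without the mediators was 80–82% throughout.

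| Mediated share | Group coefficient (SD) | Power with mediators in model |
|---|---|---|
| 0% | 0.40 | 92–98% |
| 25% | 0.30 | 71–84% |
| 50% | 0.20 | 37–50% |
| 75% | 0.10 | 14–15% |
| 100% | 0.00 | about 6% |

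**The case against.** The strongest reply is that one generic sentence is being read too closely. Section 2.10 does not say that all 14 variables enter one model, nor that this model answers objective 3; it can be read as an analysis of determinants. Group is the design factor, and a condensed article may leave covariate selection to a fuller plan. The t-test or Mann–Whitney test would still give an unadjusted total contrast, and section 2.11 openly names non-randomness as the main limitation.

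Part of this stands. The absence of group from the list does not prove that it will be left out of every model, and an unadjusted contrast is available if group is taken as one of the qualitative variables, although section 2.10 does not say so. But the article does state its predictor set, and that set is wrong for the stated objective. The unadjusted test leaves differences between the historical controls and the intervention group uncorrected.

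Two stronger readings are tempting and should not be made:
- *That the adjusted analysis removes most of the effect.* Nothing is removed unless group is added beside the mediators, and the loss exceeds half only if the mediated share does. The documents give neither a share nor a correlation. Sleep, screens, appetite regulation and active play are intervention targets in section 2.7 but are not in the list, so part of the effect may bypass it. The steep power losses in step 4 need equal shifts at 1 and 2 years; with a half-size shift at 1 year, little or no power is lost at r = 0.8.
- *That maternal BMI is entered twice.* Section 2.8.1 lists a continuous and a categorical form, but nothing says that both enter the same model; each may serve the descriptive or bivariate analyses.

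**Conclusion.** The point holds as a badly fixed analysis of the main objective. No analysis stated in the protocol estimates the total group effect adjusted for baseline differences: the multivariable model either has no group term or conditions on post-baseline variables, and the remaining test is unadjusted.

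That conclusion rests on the text alone. Its numerical size does not. Attenuation ranges from none to all with the mediated share, and would be complete only if the hypothesis in section 1 were taken literally and the whole effect ran through the listed factors. The power figures depend on the assumed 0.40 SD effect and on the assumed correlations and paths; they illustrate the range and do not predict the trial's result.

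**What to change.** In section 2.10, state one primary model: a Gaussian generalized linear model for % fat mass at 2 years, and the same model for BMI, with study group as the tested term. Adjust only for covariates fixed before the intervention can act or unaffected by it: maternal BMI at weeks 4–7 as a continuous value, child sex, and exact age at the 2-year measurement. Report the group difference with its 95% confidence interval.

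Take the post-baseline factors and BMI at 1 year out of this model. Compare them between groups as intermediate outcomes, and label any model that contains them a mediation analysis. Section 2.8 should separate baseline covariates from intermediate outcomes.

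Do not adjust for pediatric quota. Controls come from two quotas and the intervention group from four (sections 1 and 2.4). If the two are among the four and intake is even, only about 127.5/2 ≈ 64 intervention children inform the contrast, and the standard error rises by √[(1/85 + 1/63.75)/(1/85 + 1/127.5)] = √1.4 ≈ 1.18, or 18%. If they lie outside the four, quota and group are fully confounded.

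The cost is wording in sections 2.8 and 2.10. No further participants are needed, and no new data provided that birth and visit dates are recorded, as is to be expected in routine records.
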